## Abstract

**Background:**

Prescription digital therapeutics are software-based disease treatments that are regulated by the US Food and Drug Administration; the reSET-O prescription digital therapeutic was authorized in 2018 and delivers behavioral treatment for individuals receiving buprenorphine for opioid use disorder. Although reSET-O improves outcomes for individuals with opioid use disorder, most of the therapeutic content is delivered as narrative text. PEAR-008 is an investigational device based on reSET-O that uses an interactive, game-based platform to deliver similar therapeutic content designed to enhance patient engagement, which may further improve treatment outcomes.

**Objective:**

We aim to investigate how participants interact with the prescription digital therapeutic’s new content delivery format. Secondary objectives include evaluating treatment success, symptoms of co-occurring mental health disorders, recovery capital, and skill development.

**Methods:**

Due to the COVID-19 pandemic, this study was redesigned using a decentralized model because it was not possible to conduct medication initiation and study visits in person, as initially intended. A decentralized, randomized controlled trial design will be utilized to compare patient engagement with PEAR-008 and that with reSET-O using both subjective and objective assessments. The study population will consist of approximately 130 individuals with opioid use disorder (based on Diagnostic and Statistical Manual of Mental Disorders 5 criteria) who have recently started buprenorphine treatment for opioid use disorder. Participants will be virtually recruited and randomly assigned to receive either PEAR-008 or reSET-O. All study sessions will be virtual, and the duration of the study is 12 weeks. The primary outcome measure of engagement is operationalized as the number of active sessions per week with either PEAR-008 or reSET-O. (An active session is any session that contains some active participation in the app, such as navigating to a different screen, engaging with a learning module, or responding to a notification.) Subjective dimensions of engagement will be assessed with participant surveys. The hypothesis is that PEAR-008 will have significantly greater participant engagement than reSET-O.

**Results:**

As of February 2021, participant enrollment is ongoing.

**Conclusions:**

This randomized controlled trial will investigate if changing the delivery format and enhancing the content of a prescription digital therapeutic for opioid use disorder will affect how participants use and interact with the prescription digital therapeutic. The study design may serve as a useful model for conducting decentralized studies in this patient population.

**Trial Registration:**

ClinicalTrials.gov NCT04542642; https://clinicaltrials.gov/ct2/show/NCT04542642

**International Registered Report Identifier (IRRID):**

DERR1-10.2196/32759

## Introduction

### Background and Rationale

The United States is in the midst of an opioid overdose epidemic [1,2]. Underlying opioid use disorder is a key driver of this epidemic, and approximately 1.6 million people in the United States met criteria for opioid use disorder in 2019 [3]. Opioid use disorder is a chronic disease with a range of physical, psychological, and personal consequences, including high mortality. Opioids are particularly hazardous due to the rising prevalence of potent illicit opioids (predominantly fentanyl) with high risk of lethality [4]. During the COVID-19 pandemic, overdose deaths surged to an all-time high of 92,183 in the United States, driven primarily by synthetic opioids [1]. Maximizing the impact of effective therapies that are easily accessible during the pandemic and beyond is critical to helping individuals with opioid use disorder receive optimal and necessary care.

Pharmacologic treatments, such as US Food and Drug Administration (FDA)–approved medications (for example, buprenorphine, naltrexone, and methadone), are the first line of treatment for opioid use disorder, in conjunction with evidence-based behavioral therapies, but the majority of individuals in need of treatment (80% to 90% [2,5,6]) for substance use disorders do not receive care. There are a variety of contributing factors, including refusal to seek treatment, high cost of care, stigma associated with care, homogeneity of treatments offered, and lack of or limited access to treatment [7,8]. For individuals with opioid use disorder who do seek treatment, there is significant variability in quality and utilization of evidence-based therapies across providers [9,10]. Significant training, time, and clinical oversight are required to ensure proper face-to face delivery of behavioral therapy [11]. Digitizing and offering evidence-based therapies on mobile devices can standardize care, ease the burden on clinical staff, and expand access to behavioral treatment.

Prescription digital therapeutics are software-based treatments that have been evaluated for safety and effectiveness in randomized clinical trials and authorized by the FDA. Prescription digital therapeutics have the potential to safely expand access to evidence-based interventions because they are delivered on mobile devices and are prescribed and initiated by treatment providers.

Two prescription digital therapeutics are currently available—reSET and reSET-O—to deliver digitized behavioral therapy for substance use disorder and opioid use disorder, respectively [12,13]. Both prescription digital therapeutics deliver therapy modeled on the community reinforcement approach, which is an evidence-based treatment that promotes behavioral change [14]. Although studies indicate prescription digital therapeutics hold promise in treating substance use disorder and opioid use disorder [15-20], the current content delivery method used by these prescription digital therapeutics is largely didactic, with the majority of content delivered as narrative text. PEAR-008 is an investigational device that delivers therapeutic content similar to reSET-O via an interactive game-like environment designed to maximize patient engagement and satisfaction—factors that are critical in retaining patients in opioid use disorder treatment [21-26]. We hypothesize that the use of a more interactive and engaging platform to deliver similar therapeutic content will enhance patient engagement with a digital therapeutic.

## Methods

### Overview

We will compare reSET-O to PEAR-008 and evaluate objective differences in participant engagement with each digital therapeutic. Secondary outcomes include subjective differences in engagement, opioid use disorder treatment outcomes (ie, retention in treatment and abstinence from opioids), symptoms of common comorbid mental health conditions, including anxiety and depression, recovery supports (eg, recovery capital and resilience), and participant satisfaction with their assigned digital therapeutic. Exploratory aims include evaluating development of cognitive behavioral therapy skills and buprenorphine adherence.

### Study Design

This is a 2-arm, randomized controlled, open-label, outpatient-based study to be conducted virtually by 2 recruitment sites: the New York State Psychiatric Institute’s Substance Treatment and Research Services (STARS) program at Columbia University Irving Medical Center and the Addiction Research and Education Foundation (AREF). Study participants will be recruited from outpatient addiction specialty treatment programs and individual providers in the United States.

### Study Population and Sample Size

The trial will include 130 adults aged 18 to 60 years with opioid use disorder who are already receiving buprenorphine treatment, with no criteria regarding gender identity, race, or ethnicity.

Inclusion criteria are having the ability to provide informed consent, age 18 to 60 years, having adequate English proficiency, being within the first 120 days of starting buprenorphine, receiving buprenorphine pharmacotherapy under the care of a licensed health care provider and being willing to provide the name of the provider or practice, being capable of using common software apps on a smartphone, and having access to an internet-enabled smartphone that meets minimal operating system requirements for the duration of the study. Exclusion criteria are having a history of reSET-O use, having participated in user-testing of PEAR-008 or any investigational drug trials within 30 days of trial enrollment, or currently receiving methadone or naltrexone pharmacotherapy.

The sample size and power were based on the primary engagement outcome, determined by frequency of interaction with the intervention, percentage of module completion, and approval ratings. A sample size of 130, α=.05, and power=0.80 will allow for detection of a moderate effect size (*d*=0.50).

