### Randomization and Blinding

Following informed consent, the baseline assessment and confirmation of eligibility, participants will be randomly assigned to 1 of 2 treatment groups: reSET-O or PEAR-008. Randomization lists will be prepared by the study sponsor (Pear Therapeutics) prior to the start of the study. Randomization will be 1:1 and stratified by site and gender with a block size of 10. An electronic list of IDs, access codes, and credentials will be securely provided to the sites. There will be no blinding; this is an open-label study.

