#### Medical and Medication History

Medical history and current medical conditions, with current or prior treatment received, such as mental health disorders, hepatitis C virus, human immunodeficiency virus, and chronic pain syndromes, will be collected at the baseline session. Participant-reported history of substance use will be collected for the following substance categories: opioids, cocaine, stimulants (other than cocaine), alcohol, marijuana, benzodiazepines, other. Data to be collected regarding each substance include age at onset of use, number of years used regularly, amount used, type used (eg, pill vs powder), route of administration, history of overdose, and longest period of abstinence. Participant-reported history of substance use treatment will be collected, including present and prior treatment, type of treatment facility, number of treatment episodes, and current recovery activities. Nicotine use history will also be collected, including type, route, quantity, duration of use, and prior use. Medication history will include the name, dose, frequency, start and stop dates of the medication, and the indication for use. Prior or current medication for substance use disorder and opioid use disorder will also be recorded.

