### Clinical Assessments

#### Abstinence From Opioids and Buprenorphine Adherence

Participant self-report of substance use and medication adherence will be collected within the reSET-O and PEAR-008 apps. In PEAR-008, participants are prompted to report use or abstinence each time they open the app as part of the check-in feature. In reSET-O, participants are prompted to report substance use or abstinence every 72 hours and can choose to self-initiate responses anytime.

Timeline followback will be completed at each virtual study session to assess patient-reported substance use since the time of the last assessment. The timeline followback is a validated calendar-based assessment used to obtain self-reports of amount and frequency of substance use retrospectively, using memory aids to enhance recall (eg, patterns of use, key dates).

Participants will self-administer a 12-panel saliva drug test during video sessions with study staff, who can assist in proper administration in addition to providing high-fidelity confirmatory testing. The 12-panel tests detect the presence of the following drugs: amphetamines, cocaine, cannabis, opioids, methamphetamine, barbiturates, benzodiazepines, buprenorphine, oxycodone, methadone, fentanyl, and alcohol. Saliva drug testing will be performed at the baseline session, once weekly during weeks 1-8 of the treatment phase and at the week 12 follow-up session. Participants will receive drug screening equipment regularly by mail.

When available, results of urine drug screening collected as part of routine care at participating treatment centers will also be used for participants recruited by AREF. All urine drug screen data are collected for clinical purposes and not as a study procedure. Urine drug screen results will be exported from the electronic medical record for inclusion in the study database. These data will be used to evaluate buprenorphine adherence and drug use. Results from additional urine drug screen confirmatory analyses for buprenorphine and norbuprenorphine may be available for some participants. When available, these data will be used to evaluate buprenorphine adherence.

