#### Secondary Endpoint Analysis

Abstinence will be self-reported by patients via timeline followback and assessed as the absence of opioids (except buprenorphine) on saliva drug screens. Data on abstinence (binary yes and no) will be evaluated with the 9 possible saliva drug screens and urine drug screen and timeline followback data at weeks 1-8 and week 12. Differences between the treatment arms in abstinence will be assessed with a generalized estimating equation analysis using the binomial abstinence outcome as the dependent variable, assessment time, treatment, and the interaction between assessment time and treatment as fixed effects and subject as a random factor. This generalized estimating equation will be compared to a second generalized estimating equation without a treatment term using a likelihood ratio test to evaluate the impact of treatment. A treatment responder analysis will also be conducted, with a treatment responder defined as someone with ≥80% of all saliva drug screens and urine drug screens and timeline followback reports negative for all nonprescribed opioids over the course of the trial.

Treatment retention will be measured as time to dropout (number of days from baseline to last face to face contact) and analyzed using the Kaplan Meier method followed by a log rank test to compare treatment groups.

Patient assessments of recovery capital (Brief Assessment of Recovery Capital–10) resilience (Connor-Davidson Resilience Scale–10) and severity of co-occurring psychiatric symptoms (Patient Health Questionnaire–8 and Generalized Anxiety Disorder Questionnaire–7) will be evaluated with a repeated measures mixed model in a manner consistent with the primary endpoint.

Participants’ use patterns with PEAR-008 and reSET-O will include total time engaged, number of lessons and chapters completed, number of lessons and chapters repeated, number of completed self-report assessments, and response to notifications. Descriptive statistics of each treatment arm will be summarized and differences between PEAR-008 and reSET-O will be assessed with a *t* test (or its nonparametric alternative if the distributional assumptions are violated).

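### The abstinence model leaves out baseline opioid status and time on buprenorphine, which costs precision and leaves chance imbalance unadjusted, though the comparison stays unbiased

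*Protocol article*

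**What the plan says.** All references are to the protocol article.

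- **Who enters.** Study Population and Sample Size describes adults "who are already receiving buprenorphine treatment" and sets the entry window as "being within the first 120 days of starting buprenorphine".
- **How they are allocated.** Randomization and Blinding places allocation after the baseline assessment and states: "Randomization will be 1:1 and stratified by site and gender with a block size of 10". Neither time on buprenorphine nor baseline drug-test result is a stratification factor.
- **What is known before allocation.** Abstinence From Opioids and Buprenorphine Adherence states: "Saliva drug testing will be performed at the baseline session". Medical and Medication History records the "start and stop dates of the medication" at the baseline session.
- **How abstinence is analysed.** Table 1 determines abstinence nine times, in weeks 1 to 8 and week 12, so the baseline test is not one of the outcomes. Secondary Endpoint Analysis lists the model terms as "assessment time, treatment, and the interaction between assessment time and treatment as fixed effects and subject as a random factor". This model is then compared with one that has no treatment term. No baseline covariate is named there or in the responder analysis.

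**The concern.** A patient a few days into buprenorphine and a patient nearly four months in may differ a good deal in their chance of an opioid-negative week. So may patients who test positive and negative at baseline, since the baseline screen uses the same test as the outcome. If so, much of the between-patient variation in abstinence is predictable from data already in hand at randomisation, and the stated model leaves it as noise.

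Two things are at stake:

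- **Precision.** The sample size was set on engagement, so abstinence has no power calculation of its own to absorb the loss.
- **Interpretation of a chance imbalance.** The trial is open-label. If the arms happen to differ in baseline-positive share, covariates chosen after that is seen are open to challenge. Covariates fixed beforehand are not.

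**Working it through.** **1. The plan's own figure.** The article states N = 130, α = .05, power 0.80 and d = 0.50 for engagement. Sidedness is not stated, so two-sided is assumed.

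- Normal approximation: n per arm = 2(1.960 + 0.842)² / 0.50² = 62.8, so 63 per arm and 126 in total.
- Two-sample t test: 63.8, so 64 per arm and 128 in total.
- Power at 65 per arm: 0.813 (normal) or 0.808 (t test).

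The stated 130 is sound for engagement. No figure is stated for abstinence.

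**2. Expected chance imbalance at 65 per arm.**

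- Baseline-positive share, SD of the arm difference = √(2p(1−p)/65). With p assumed at 0.30 this is 8.0 percentage points, and with p = 0.50 it is 8.8. A gap beyond 1.96 × 8.0 ≈ 16 to 1.96 × 8.8 ≈ 17 points would occur in about 1 trial in 20.
- Mean days on buprenorphine, assumed uniform over 0 to 120: SD of the arm difference = (120/√12) × √(2/65) = 6.1 days.

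**3. Simulation of the abstinence comparison.** The documents give only the two arms at 1:1, N = 130, nine binary assessments and the 120-day window. Everything else is assumed:

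- days on buprenorphine uniform over 0 to 120;
- about 35% positive at baseline, less likely with longer time on buprenorphine;
- patient random effect with SD 1.0;
- conditional treatment log odds ratio 0.8 (odds ratio e^0.8 ≈ 2.2).

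The analysis was logistic with independence working correlation and patient-clustered robust variance, fitted with treatment alone and then with treatment, baseline result and days. There were 3,000 runs under no effect and 2,000 under the assumed effect per scenario. Prognostic strength is given as the log odds ratio for a positive baseline test, then for each 60 days on buprenorphine.

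| Prognostic strength | Type I error, unadjusted / adjusted | Power, unadjusted / adjusted | Power lost | Mean estimate under the effect, unadjusted / adjusted |
|---|---|---|---|---|
| None (0, 0) | 0.048 / 0.049 | 0.93 / 0.93 | 0 | 0.67 / 0.68 |
| Moderate (1, 0.3) | 0.052 / 0.058 | 0.90 / 0.94 | 4 points | 0.65 / 0.68 |
| Strong (2, 0.5) | 0.052 / 0.055 | 0.74 / 0.93 | 19 points | 0.56 / 0.68 |
| Very strong (3, 0.5) | 0.053 / 0.052 | 0.52 / 0.92 | 40 points | 0.49 / 0.69 |

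Under no effect, the mean estimate was within 0.01 of zero in every scenario, adjusted or not. The Monte Carlo standard error of a type I error near 0.05 is √(0.05 × 0.95/3000) = 0.004, so all the values are compatible with 0.05.

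**4. What this shows.** Leaving the variables out does not disturb the validity of the test. Including them lost no power when they were uninformative and gained power when they were prognostic. The smaller unadjusted estimates in the lower rows reflect the marginal odds ratio lying closer to 1 than the conditional one. That is a different estimand, not bias.

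**The case against.** **An unadjusted randomised comparison is valid.** This stands. A reader might infer that differences in stage of treatment could mimic a treatment effect. The documents do not support that: allocation is randomised 1:1 after baseline, so stage differs between arms only by chance, and the significance level already covers it. The simulated type I error of about 0.05 agrees.

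**The wide entry window is not itself a defect.** This also stands. A reader might infer that patients negative at baseline have no room to improve. But abstinence is a weekly status, not a change score, so such patients can relapse and still carry information. Nor is it a fault that study week differs from week of buprenorphine treatment. The randomised intervention is the app, installed after randomisation, and study week is the right clock for it.

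**The size is assumed.** This stands too. The documents give no prognostic strength. The large losses need log odds ratios of 2 to 3 for the baseline test (odds ratios of about 7 to 20). An effect of 0.8 may be generous for two apps with similar content and the same reward odds. The simulation tested a treatment main effect averaged over the nine assessments, not the article's comparison of models with and without treatment terms, so the percentages are illustrative.

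**An unseen SAP may add covariates.** This stands only in part. Secondary Endpoint Analysis names the model's terms one by one and does not defer them. If the SAP adds covariates, it departs from the published model and the two should be aligned.

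**Conclusion.** The point holds as a matter of efficiency, not validity. As written, the abstinence GEE uses neither of two plausible predictors that are recorded before randomisation. With the assumptions above, the cost in power runs from nothing through about 4 points to about 19 to 40 points. Where the trial falls in that range cannot be settled from the documents.

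The choice is lopsided, because adjustment cost no power at the bottom of the range and kept type I error near 0.05 throughout. That, rather than any single power figure, is the reason to change the plan.

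The reach is limited. Abstinence is one of several secondary outcomes, and neither the engagement endpoint nor N = 130 is touched. The calculation covers abstinence only. It gives no figure for retention or adherence.

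**What to change.** - **Abstinence.** Prespecify as covariates in both models being compared: baseline opioid status, days from buprenorphine start to randomisation, and the stratification factors site and gender. Define baseline status from the saliva screen, together with timeline followback if it is taken at the baseline session. Site and gender were not in the simulation; they are included because they were used to stratify.
- **Adherence (exploratory GEE).** Use the baseline buprenorphine result, which is in the saliva panel, and days on buprenorphine. Baseline opioid status is not the natural covariate for that outcome.
- **Retention.** Optionally report a covariate-adjusted Cox model as supportive, beside the planned log-rank test.

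The change should be dated and made before outcome data are compared by arm. It needs no new data and no change to eligibility or procedures. It costs a few degrees of freedom, and the odds ratio becomes conditional on the covariates. The report should say so.

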### Study Settings and Recruitment Procedures

All study sessions will be conducted virtually by study staff at 2 participating organizations: New York State Psychiatric Institute’s STARS and AREF.

Since its establishment in 1997, the STARS clinic of Columbia University has served as the center for clinical trial operations within the Division on Substance Use Disorders. Recruitment will be directed to individuals who live in New York, New Jersey, and Pennsylvania. Participants may be recruited via flyers in office spaces or intake packets (as allowed; flyers will be disseminated electronically to providers and opioid treatment programs) or via word of mouth by providers. In addition, potential participants may be referred to this study after screening procedures conducted in concurrent research studies taking place at STARS (eg, if they are ineligible for concurrent studies, they may be referred to this study for screening).

AREF is a research foundation that conducts and disseminates research related to addiction medicine to advance the science surrounding the treatment of individuals with a substance use disorder. AREF conducts research activities with patients recruited from a multistate network offering guideline-driven outpatient treatment with buprenorphine for individuals with opioid use disorder in a group practice setting. When possible, flyers will be posted in the waiting room at treatment locations (where patients are being seen face-to-face, which is dependent on local regulations related to COVID-19). Flyers will be included in patient packets that are emailed or distributed to new patients. Additional participants may also be recruited via online advertisements (eg, Craigslist).

Participant flyers will provide the URL for the study website as well as a QR code to access the website. On the study website individuals will find information about the study and a form to express interest in participating in the study. Data entered on the website are sent to an encrypted database housed by Formstack, a Health insurance Portability and Profitability Act–compliant platform and to the sites via PGP-encrypted emails.

